### 6.6 Claim 6: brain regions evolve with age

We hypothesize that with age we will find more reciprocal conversational behaviors, as children become more able to participate in interpersonal synchrony, and increasingly able to develop abstract shared mental representations with others, leading to greater IBS. We expect to find IBS particularly in the TPJ for the younger age groups and in the PFC in the older age groups (Dumas et al., 2020). In the absence of prior research concerning the development across middle childhood of the neural correlates of social bond formation, we propose to study IBS across the 4 age groups in relationship to the task (solo vs. collaboration vs. discussion). To that end, following Wang et al. (2022), a GLM model will be used to estimate changes in IBS values across ROIs, pairs, and distinct experimental phases. To ensure robust statistical inference, False Discovery Rate (FDR) correction will be implemented. We believe that the identification of developmental dynamics in IBS will provide valuable insights into the critical cognitive processes at play in rapport, and will thus potentially play a role in guiding the design of interventions.

## 7 Modeling productive conversational behaviors in virtual peers

With advances in end-to-end machine learning models of conversation, the promise of usable virtual reality solutions for work and play in the Metaverse, and the introduction of large language model (LLM) chatbots, there has been a renewed focus on building embodied conversational agents (ECAs), i.e., conversational agents with computer-generated animated bodies that are displayed on a screen and that can both recognize and display language and non-verbal behavior to communicate with their human interlocutors. These systems are targeting challenges as varied as adherence to medical treatment (Bickmore et al., 2010; Tudor Car et al., 2020), lifestyle changes (Kramer et al., 2020), education (Lane and Schroeder, 2022), and even daily home tasks where individuals could benefit from the support of a personal assistant (Pham et al., 2018). However, a stumbling block in the implementation of systems that can engage with their users for more than a minute or two is the implementation of the kind of appropriate rapport-building social interaction strategies that in human interaction underlie successful collaborative task performance, and that are more sophisticated than simple meaningless chit-chat. Such strategies are particularly important for educational interactions where children in the classroom and in informal learning contexts constantly intersperse task and social talk, and where, as we described above, reasonable amounts of apparently off-task social talk has been demonstrated to improve collaborative learning (Madaio et al., 2017a). The study proposed here therefore has both basic science goals, identified above, and a translational motivation, which is to build more effective Embodied Conversational Agents (ECAs) for education. The design of ECAs and specifically of virtual peers (ECAs that look and behave like children) has relied on studies of real children, including our own work on peer collaborative learning (inter alia; Madaio et al., 2017a; Cassell, 2022). The use of neuroscientific data to enhance the learning properties of ECAs has not been studied, however. In fact, the majority of studies that look at neural activation in the context of virtual agents has been restricted to people *viewing* agents and not interacting with them. Exceptions are our lab's early work comparing brain activation in individuals interacting with a human MRI technician vs. an ECA MRI technician, in two conditions: where the technician (human or ECA) simply explained the MRI, or also engaged in social interaction. In the task-only condition, increased superior temporal gyrus activation was found for the virtual human technician over the real technician. For the social interaction condition, on the other hand, interaction with both the real and virtual technicians resulted in increased activation in areas associated with social cognition, but there was greater activation for the human technician (Gayda et al., 2008). More recently, work by Chaminade et al. (2018a,b) has compared interaction with a virtual head to interaction with a person, and shown increased activation in the TPJ for the interaction with a human. However, the virtual head used in the experiment was quite limited in its expressiveness and was piloted by a “wizard” rather than being driven by human-human data. We have also found increased involvement of the rTPJ during social coordination between individuals and a virtual partner represented by the human dynamic clamp (Dumas et al., 2020).

The study outlined here is designed to better understand the relationship among conversational behaviors, rapport and IBS in pairs of children, in the context of an education-oriented task. In so doing it may thus show us the path to implementing a more effective VP, an AI system that looks (see Figure 3) and acts like a child, and that engages children in a set of conversational behaviors that can be shown to lead to productive rapport, and hence to learning gains. Implementing these behaviors in a VP gives us a way of evaluating our basic science results: do the behaviors that seem most effective in analysis turn out to be the most effective in synthesis? In the past our ECAs and VPs have always served this double role: a system that can play positive role in children's lives, and serve as a tool for better understanding the use of multimodal behaviors in interaction. In this sense, as described above, our work is tightly aligned with the goal of social neuroergonomics, that also proposes bringing together cognitive science, computer science and neuroscience in order to better understand how people engage in social interaction with one another, and how to build machines that better understand and support this interaction (Dehais et al., 2020).

**Figure 3 F3:**
[figure not shown]
Child working with a virtual peer on a math problem (for illustration purposes).

As emphasized by Cross and Ramsey (2021), then, the incorporation of human-like attributes into a non-human entity, followed by the assessment of similarity using behavioral and neural measures of human interaction, offers an important way of investigating how to improve current AI systems. In our evaluation of the resultant virtual peer, we will therefore once again collect fNIRS data. Clearly, we will not collect IBS data in this context, however we will investigate the neural correlates of interaction with VPs, and compare it to that of child-child interaction for each age group.

While a full description of how to implement such VPs is beyond the scope of this article, it is important to emphasize that new techniques in artificial intelligence make this goal significantly more attainable. In particular, we have demonstrated that we can fine-tune LLMs such as DialoGPT (Zhang Y. et al., 2020) or ChatGPT3.5 (OpenAI, 2022)—that is, feed them many instances of a particular way of talking—and that the resultant machine learning model is able to then generate appropriate social language, such as hedges in the style of teenage peer tutors (Abulimiti et al., 2023). The complete methodology is depicted in Figure 4.

**Figure 4 F4:**
[figure not shown]
Recapitulation of the methodology.

## 8 Feasibility study

In order to evaluate the feasibility of fNIRS hyperscanning over Zoom with dyads of children in this age group, and to assess the quality of the data collected in this manner, we ran a feasibility study. As we did not intend to look at performance metrics in the feasibility study, nor to gather data across multiple weeks, we chose to use a task that was familiar to children in this age range. We therefore developed a single-session paradigm based on a digital adaptation of the *Guess Who* game. *Guess Who* is a two-player board game that involves inferring an answer from a set of clues. The game has 24 possible characters with various distinguishing attributes (e.g., gender, facial hair, glasses, etc.). In the original board game, players randomly select a character card whose identity the player's opponent must guess by asking a series of yes or no questions. The children alternate between choosing a card, and asking questions of the other player to eliminate incorrect character possibilities on their game boards. In the experimental version, we adapted the game to be presented on a screen, with familiar characters from popular animated television and film that target this age group in France.

In addition to developing a digital version, we also adapted the game to allow both solo and collaborative modes. Thus, instead of asking the original game's yes-no questions about features pertaining to the character, children were given clues that were displayed one by one above the game board on the child's screen. In order to be suitable for pre-literate younger children as well as older, each clue was represented with a short one- or two-word label and a picture. In total, each character round consisted of four clues. Children were instructed to remove the characters that did not correspond to the clue by clicking on the character's image. In response, a red “X” appeared over the image of the character indicating that the character was eliminated. For example, if the clue was “*garçon”* (“boy”), the child saw a blue silhouette of a male human figure and should have eliminated all female characters. For the solo phase, this process was repeated for each of the four clues until only one final character was left un-eliminated. After only one final character remained on the board, the correct answer appeared in the middle of the screen. If the correct character was chosen, the character's image appeared outlined in green while if an incorrect character was chosen, the image was outlined in red. The game board then reinitialized, beginning again with a new set of clues leading to another character.

During the collaborative phase, on the other hand, each member of the dyad received different clues, which they had to compare and discuss with their partner, with whom they interacted via videoconference. For instance, one child may have received the clue “*sourire”* (“smile”) while the other child may have received “*garçon”* (“boy”). By sharing their clues, both children knew to eliminate all characters who were not male and not smiling. The game was designed to induce collaboration by making it impossible to correctly guess the final character without sharing clues.

After training and capping, the feasibility experiment was composed of four 7-min phases: solo task, first discussion, collaborative task, and second discussion. In order to allow for the capture of baseline neural activity, each experiment began with a 75-second baseline period, and there were 30-second baseline periods between each phase. Children were not in the same location and did not meet except by videoconference during the collaborative task and the two discussion phases. We note that while we had 5 baselines in the feasibility study, the time to explain them, set them up and focus the children added significant time to the experiment, and sitting still and staring fixedly was uncomfortable for the majority, and so we have reduced the number of baselines for the proposed study.

For the first discussion phase, the children were introduced over videoconference and it was suggested that they chat to get to know one another, and to discuss potential game strategies while the experimenters set up the next part of the experiment. The collaborative phase of the game was then played with the child peer partner, also for 7 min. During this phase the game board was presented on the left half of the screen and the videoconference featuring the other child was presented on the right half of the screen (see Figure 2A). The children's webcams were adjusted to capture their entire face and shoulders. A high-fidelity microphone captured the children's speech. Subsequently the children were instructed to chat freely while the experimenters set up the last part of the experiment. PsychoPy (Peirce et al., 2019) was responsible for maintaining the synchronization of the audio, video and fNIRS equipment.

## 9 What can we conclude from the feasibility study?

Five dyads of children participated, based on recruitment among local researchers and the social media accounts of a local babylab. The children in one dyad turned out to know one another beforehand, however they and the other four dyads were able to complete the task, and the data of all five are of high quality, and are included in the feasibility study analyses reported here. The five dyads are composed of 2 dyads of boys and 3 dyads of girls. The children had an average age of 10.2 years, with a standard deviation of 1.4 years.

As described in the Supplementary material, analyses conducted on HbO values showed that IBS was significantly greater during the two interactive phases (collaboration and social) than during the solo phase, specifically in the right TPJ (Figure 5A). As evidence that the presence of IBS is due to social interaction and not to looking at the same stimulus materials, during the initial discussion period, IBS for the rTPJ was significantly higher for the authentic dyads than for the random pairing of children (Figure 5B). These results resemble those found in parent-child pairs, for example in Nguyen et al. (2020), as well as for adults in similar situations (Jiang et al., 2012). The fact that the STS did not demonstrate significantly higher IBS in the collaboration or discussion phases than in the solo phase, as has been found in a number of studies looking at perception of faces (e.g., Lee Masson and Isik, 2021), may result from the videoconference set-up where, for example, it is more difficult to assess whether the other person is meeting one's gaze. This suggests that data collected in a face-to-face condition with fewer children should also be included during the proposed study in order to ensure that data collected via videoconference is substantially similar to that collected face-to-face.

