### 4.1 Target population and sample

An *a priori* power analysis was conducted using G^*^Power 3.1.9.7 (Faul et al., 2007) to determine the sample size needed for the study. The analysis was based on an ANOVA with 4 age groups and 6 measurements, using an effect size of (d = 0.24), based on our pilot study results, and an alpha of 0.05. The results indicate that a total sample size of 176 dyads will be required to achieve a power of 0.95. This aligns with the recommendation of Bizzego et al. (2022), who suggested a minimum sample size of *N* = 150 to detect significant IBS. There are significant challenges in recruiting participants for hyperscanning experiments, and particularly for recruiting dyads of unfamiliar children. In the event of a smaller sample size, we can adopt an analytical approach, such as the non-parametric bootstrap test with a pooled resampling method, as proposed by Dwivedi et al. (2017), and cited in Bizzego et al. (2022), which has demonstrated satisfactory performance in cases of small sample sizes and non-normally distributed data. We will enlist equal numbers of dyads from 4 age groups: 5–6, 7–8, 9–10, and 11–12 years (44 dyads per group). As social interaction may differ between boys and girls at these ages (Underwood et al., 1999), dyads will be of the same gender (both boys or both girls), and half of our participants will be male and half female (88 dyads of girls and 88 dyads of boys). As described above, in order to assess the initial building of rapport, all children will be strangers to one another. Our videoconference set-up will facilitate this, as we will set up video-conferencing in 2 different schools or after-school programs.

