## 11 Discussion

By integrating the four types of data described above, we aim to gain a deeper understanding of how pairs of children deploy conversational behaviors to establish bonds during middle childhood, a developmental stage characterized by a heightened focus on peer interaction. This integrated approach can also shed light on the neural processes involved in the development of interpersonal rapport over the course of a budding relationship, and the development of rapport-building over the course of middle childhood, as well as the role of rapport in educational performance. We also argue that a better understanding of these mechanisms can play a translational role in improving technologies for education, in particular the development of virtual peers, artificial intelligence partners in learning. To achieve the goals laid out above, we propose a novel multimodal approach using hyperscanning via functional near-infrared spectroscopy to study the neural, behavioral, psychological and performance correlates of rapport in middle childhood, during remote social and task exchanges in an ecologically-valid context of collaboration. While literature directly addressing our topic is limited, an extensive review of literature in social neuroscience and concerning children's multimodal conversational behavior, and interpersonal bond formation allows us to formulate guiding hypotheses. Additionally, a feasibility study demonstrates our ability to collect high-quality hyperscanning data from children engaged in videoconference collaboration and conversation, and to analyze its relationship to these other types of data.

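### The pilot offers no fNIRS quality evidence for 5–6-year-old dyads, and Claim 6 compares IBS across ages without a signal-quality check, so a rise with age could be partly artefact

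*Protocol article*

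**What the plan says.** Section 8 gives the pilot's purpose: "In order to evaluate the feasibility of fNIRS hyperscanning over Zoom with dyads of children in this age group". Checking data quality was its other declared aim. Section 9 reports that "Five dyads of children participated" and that "the data of all five are of high quality, and are included in the feasibility study analyses reported here". It gives the ages only as a mean and SD ("The children had an average age of 10.2 years, with a standard deviation of 1.4 years") and no quality measure by age or channel. The Discussion (section 11) concludes that "a feasibility study demonstrates our ability to collect high-quality hyperscanning data from children".

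The main study is wider in age. Section 4.1 says: "We will enlist equal numbers of dyads from 4 age groups: 5–6, 7–8, 9–10, and 11–12 years (44 dyads per group". Section 4.2 mentions successful piloting with 5–6-year-olds, but of the tasks, annotation schemes and performance metrics; fNIRS is not named there.

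Claim 6 (sections 3 and 6.6) predicts more reciprocal behaviours with age, greater IBS, and a shift from rTPJ to PFC. For the test, section 6.6 says that "a GLM model will be used to estimate changes in IBS values across ROIs, pairs, and distinct experimental phases", applied across the four age groups with FDR correction. No term for signal quality, retained channels or motion is named.

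**The concern.** IBS is measured by wavelet coherence between two recordings. Noise that is independent between the two children lowers coherence even when true synchrony is unchanged. If cap fit or movement makes recordings poorer in younger children, their measured IBS falls, which is the direction Claim 6 predicts for the overall level. The article itself observes that children may find it hard to keep still (section 3), that head size varies (section 5.1), and that sitting still for baselines was uncomfortable for most pilot children (section 8), who averaged about 10 years. With no 5–6-year-old dyad recorded, there is nothing to show whether such a gradient is negligible. At stake is the reading of an age trend in IBS as development.

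**Working it through.** **The plan's own figures.** 176 dyads / 4 groups = 44 per group, as stated. Reading 0.24 as Cohen's f, with 4 groups, 6 measurements and an assumed correlation of 0.5, the power of the between-group test at 176 dyads is 0.948, close to the stated 0.95. The sample size is thus consistent with one built on the age comparison. The article gives no figure for signal quality by age.

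**Pilot ages.** Inputs from section 9: n = 10 children, mean 10.2, SD 1.4. If j children are at age a or younger and d = mean − a, the smallest possible sum of squares is j·d² + (j·d)²/(n − j).

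- Available: 9 × 1.4² = 17.64 (divisor n − 1) or 10 × 1.4² = 19.6 (divisor n).
- Two children at 7, d = 3.2: 2 × 10.24 + 6.4²/8 = 20.48 + 5.12 = 25.6. Not possible.
- Most lenient rounding (mean 10.15, SD just under 1.45): 24.8 needed, at most 21.0 available. Still not possible.
- If the SD is over five dyad means: 10.24 + 10.24/4 = 12.8, a minimum SD of 1.79 or 1.60 against 1.4. Not possible.
- Youngest age both members of one dyad could share: 10.2 − √(17.64/2.5) = 7.5, or 10.2 − √(19.6/2.5) = 7.4 (7.25 at the most lenient rounding).
- Two dyads under 9, d = 1.2: 4 × 1.44 + 4.8²/6 = 9.6, possible. Three dyads: 6 × 1.44 + 7.2²/4 = 21.6, not possible at the stated figures.
- One child alone could be as young as 10.2 − √(19.6/1.111) = 6.0.

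**Effect of unequal noise (illustrative).** Let s be the share of a child's in-band variance that is signal. With independent noise, squared coherence is multiplied by s for each child, so by s² in a dyad. Suppose true synchrony is equal at all ages.

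- Shares 0.74, 0.76, 0.78, 0.80 from youngest to oldest: the youngest fall to 0.74²/0.80² = 0.856 of the oldest.
- Shares 0.77, 0.78, 0.79, 0.80: 0.77²/0.80² = 0.926.

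Estimated coherence also has a floor that noise does not lower. With the floor as a fraction φ of the oldest group's IBS, relative IBS = φ + (1 − φ)·s²/0.80². The table gives the probability that a one-way test of age (44 dyads per group, alpha 0.05, noncentral F, SD = CV × mean IBS) is significant although no true age effect exists.

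| Shares | Between-dyad CV | φ = 0 | φ = 30% | φ = 50% |
|---|---|---|---|---|
| 0.74–0.80 | 20% | 91% | 57% | 30% |
| 0.74–0.80 | 40% | 33% | 17% | 10% |
| 0.77–0.80 | 20% | 32% | 17% | 10% |
| 0.77–0.80 | 40% | 11% | 8% | 6% |

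Shares, CVs and floors are assumptions; none is in the article.

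**Does z-scoring against the solo phase (section 5.2.2) remove this?** In a simulation with fixed true coupling and ordinary spectral rather than wavelet coherence, solo coherence stayed near 0.10. Interaction coherence was 0.271, 0.231, 0.194 and 0.151 at signal-to-noise ratios of 10, 4, 2 and 1, and the z-score fell from 5.9 to 4.8, 3.3 and 1.6. Z-scoring does not remove the effect. The floor there was about 35% of the interaction value at a ratio of 10 (0.096/0.271) and 43% at 4 (0.099/0.231), so the zero-floor column is the unfavourable extreme.

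**The case against.** Six arguments weigh on the other side.

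- **A condensed article may leave nuisance covariates to the full plan.** Section 6.6 excludes none, and their absence alone would be no defect. The point rests on the combination: a stated age comparison, a predicted direction that noise could imitate, and quality evidence that misses the youngest band.
- **The pilot is not misreported.** A reader might infer that the authors claim proven signal quality in 5–6-year-olds. They do not. Section 8 states a purpose, section 11 names no age range, section 9 gives the ages, and section 10 says the pilot is too small for conclusions about child-child interaction.
- **There are many safeguards.** Visual inspection, short-channel regression, motion correction, the 0.8 scalp-coupling (SCI) cut-off, the shared-channel rule and optode digitisation (sections 5.1 and 5.2), together with the random and shuffled pairs of section 5.2.2, all help. They clean or screen data, localise channels, or test IBS against chance. None makes residual noise equal across ages.
- **The direction is assumed.** Shared motion or systemic artefact could raise IBS in younger dyads instead. This stands.
- **Adjustment can overcorrect.** The article treats movement synchrony as part of bonding (section 2) and cites body movement as preceding IBS (section 6.3). Quality may also be collinear with age. This stands, and argues against making survival on adjustment an absolute condition.
- **Collection is staged.** Section 4.2 starts with 9–10-year-olds, which leaves time to check younger children. This is true, but no such check is stated.

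**Conclusion.** The concern holds in a limited form. It is certain, from the article's own figures, that no pilot dyad had both children under 7; the evidence for 7–8-year-olds is at most two of five dyads under 9 at the stated figures. It is also clear that the Claim 6 comparison, as described, has no signal-quality term and that the existing steps do not equalise residual noise.

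That the predicted IBS rise could be partly artefact is conditional on noisier recordings in younger children, for which the article gives no data either way. The false age effect then ranges from about 91% to 10% of studies (shares 0.74–0.80) or 32% to 6% (shares 0.77–0.80), depending on CV (20%–40%) and floor (0–50%).

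Two stronger readings are not supported. Claim 6 as a whole could not be confirmed by cap fit and movement alone: poor cap contact cannot create more reciprocal behaviours, and uniform noise does not readily produce a shift from rTPJ to PFC. Nor do the figures exclude every young child from the pilot; a single 6-year-old is possible, though a 5–6-year-old dyad is not.

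**What to change.** - **Section 6.6, description.** Tabulate by age group the surviving shared channels per ROI, the mean SCI (the lower of the two children), and the share of samples altered by motion correction.
- **Section 6.6, analysis.** Report the age effect on IBS without these measures. As a prespecified sensitivity analysis, report it with surviving channels and SCI added, and separately with the motion share added, because movement may be part of the interaction.
- **Interpretation.** If an overall rise in IBS with age disappears on adjustment, describe it as possibly due to signal quality. Do not make survival an absolute condition.
- **Sections 9 and 11.** State that data quality was shown in children averaging 10.2 years and that the pilot included no 5–6-year-old dyad.
- **Section 4.2.** Use the staged start to compare the first 5–6-year-old dyads on the same measures before relying on that band.

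The cost is small. The measures can be derived from the planned pre-processing, and the rest is rewording. The price is a few degrees of freedom, and some loss of precision in the adjusted analyses if quality is collinear with age.
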